### Confidentiality

In this study, confidentiality will be rigorously protected by several procedures. The patient surveys, which will be conducted anonymously upon exiting the consultation, will be transcribed by the Recog staff into a Microsoft Excel file for subsequent analysis, without any identifying data. The audios collected during the consultations will be automatically stored in the AI-powered tool platform, guaranteeing their security by storing them in the S3 (Simple Storage Service) service of Amazon Web Services, with controlled access, encryption, and without identifiers that allow patients to be identified. The professionals’ comments will be stored in Amazon Web Services DynamoDB tables, also with controlled access, thus ensuring the confidentiality of all the information collected.

In no case is the objective of the study to train the algorithm with the data obtained, since the algorithm is already trained. The models applied are speech-to-text models, originally trained on multilingual datasets [22] and a large language model trained on generic datasets in multiple languages, public and private, not specified by the model developer. Notes are written in the project and no medical analysis is being performed by AI. The initial tests have shown the correct capability of the complete software for this task, which we seek to validate more extensively with this project. The initial stages of the algorithm use machine learning techniques, such as advanced speech-to-text models for transcription. The subsequent steps, including structuring the extracted information into relevant clinical fields, rely on a combination of rule-based processes, predefined templates, and generative AI models.

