### Relisten

In this context, the Spanish company Recog Analytics has developed Relisten [20], an automated clinical note-writing system designed to handle real-world consultations, supporting multiple languages and offering integration with EMRs.

Through a natural conversation between the health care professional and the patient, this AI-powered tool uses recordings to extract relevant fields corresponding to key sections of the medical history in a structured way and then send them to the Health Information System (after correction and approval by the health care professional). A detailed description of the algorithm’s architecture can be found in Multimedia Appendix 1, providing technical insights into its design and functionality.

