## Methods

### Study Objectives

This study has the following objectives: (1) to evaluate the perceived quality of care reported by patients with the use of an AI-powered solution in the consultation, measured through anonymous satisfaction questionnaires at the end of each consultation (Multimedia Appendix 2); (2) to assess the satisfaction of health care personnel with the care provided in consultations, measured using an anonymous satisfaction survey at the end of the study (Multimedia Appendix 3) and a structured interview; and (3) to assess the time spent by health care personnel on entering records in the EMR, measured by statistical tests comparing consultations with and without the tool.

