The measurement of the objectives will be carried out using the following methods: (1) perceived quality of care as reported by patients using an anonymous patient survey after each consultation, in a patient-blinded study (patients are not told beforehand whether the AI-powered tool has been used in the consultation; this fact is outlined by a graphic mark in the surveys in which the tool has been used); (2) satisfaction of health care personnel: an anonymous survey will be conducted at the end of the study. This will qualitatively evaluate the tool’s impact on consultations, focusing on aspects such as its general usefulness, ease of use, the quality of notes generated, its perceived ability to improve attention during consultations, and the extent to which it saves time. In addition, the study will incorporate structured interviews with primary care health care professionals (nurses and physicians) to explore their experiences with the tool in depth. The interviews will include questions about the above concepts, as well as at least an additional request to the health care professional to identify limitations and improvements to the tool. (3) Time spent entering information into the EMR. To determine the magnitude of savings, 2 measurements taken during the PoC will be compared: the time the health care professional spends typing in the consultation and the time the health care professional spends reviewing and correcting notes generated by the AI-powered tool.

Figure 1 facilitates the visualization of the development of the study in consultations.

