### Data Collection

The data collection process involves the following:

Satisfaction surveys completed by patients at the end of the consultation (with the AI-powered tool as a test and without the tool as a control). The survey will be given to the patient on paper by the health professional inside the doctor’s office at the end of the visit. They will be collected anonymously in a box upon exiting the office, in a visible and accessible place. This involves single-blinded data collection (the patient does not know whether the AI-powered tool is being used, although the health care professional does). These questionnaires will be available in Catalan and Spanish.Quality surveys at the end of each consultation by health care professionals, on a scale of 0-10 with the possibility of including open-ended comments, will be carried out directly through the AI-powered tool’s digital platform. These questionnaires will be available in Catalan and Spanish.Satisfaction surveys completed by health care professionals at the end of the study, as well as interviews to better understand the impact and limitations in a qualitative manner.Recordings of conversations between the patient and health care professional (Recog will delete the recordings at the end of the study).

These items align with study objectives and are detailed in the Multimedia Appendices 2 and 3.

Qualitative data will be collected using open-ended survey surveys for patients and health care professionals and structured interviews with professionals. These data will be analyzed using thematic analysis.

The study variables are mentioned in Textbox 1.

Study variables.

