**Dependent variables**
Results for each survey question, on a scale of 1-5.Time saved during consultations is measured by comparing the writing time in the 2 scenarios: one where doctors manually write notes during the consultation (non–AI-powered audios) and another where they review and correct notes generated by the AI-powered tool. For the non–AI-powered audios, investigators listen to the recordings and measure the exact time the professional spends writing. In AI-assisted consultations, the doctors use the platform to time their note corrections. By comparing these two measurements, the study aims to quantify the time-savings offered by the AI-powered tool, with each recording being analyzed individually for accuracy. This has been chosen because other forms of measurement (such as automatically measuring silences) may introduce greater biases (silences due to circumstances other than note taking) than human interpretation. Although logically it is not a perfect measure either, the savings impact is expected to be sufficiently significant for these random errors to have a very small impact in relative terms.In addition, health care professionals are asked to include, through the AI-powered tool’s digital platform, possibly relevant comments about the consultation they have just carried out, such as when a consultation has been carried out in multiple languages, with one participant speaking in Spanish and another in Catalan.

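### Staff of the tool's developer key the paper patient surveys with the study arm marked on the form, and no masking of that step is described

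*Protocol article*

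**What the plan says.** All references are to the protocol article.

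- **The outcome.** Study Objectives lists first "1) to evaluate the perceived quality of care reported by patients". Statistical Analysis names reported quality of care as one of two main hypotheses, and under Sample Size and Randomization it sets the total of 800 patients. The dependent variable is "Results for each survey question, on a scale of 1-5" (Dependent variables).
- **The form.** "The survey will be given to the patient on paper by the health professional" at the end of the visit. Of the completed surveys, Data Collection says: "They will be collected anonymously in a box upon exiting the office".
- **The arm on the form.** Patients are not told beforehand whether the tool was used, but "this fact is outlined by a graphic mark in the surveys in which the tool has been used" (Overview, Design, and Hypotheses of Study).
- **Who enters the data.** The surveys "will be transcribed by the Recog staff into a Microsoft Excel file for subsequent analysis" (Confidentiality).
- **Who that is.** "the Spanish company Recog Analytics has developed Relisten" (Relisten).
- **Who is blinded.** "the patient does not know whether the AI-powered tool is being used, although the health care professional does" (Data Collection). No other blinding is described.

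**The concern.** The person who turns a paper answer into a number works for the company whose product is being evaluated, and the form shows which arm it came from. The article names no other carrier of the arm on the survey, so on its account whoever builds the file has to read the mark to code the arm. Unmasked entry follows from the arrangement as described.

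This is separate from whether the patient understands the mark. Even if no patient ever notices it, the person keying does.

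At stake is the satisfaction comparison. Any tendency to read an unclear answer differently by arm goes straight into the difference in means, and a larger sample does not reduce it. The Discussion says the results will serve to validate the tool. A patient-reported result keyed unmasked by the manufacturer is easy to challenge even when every entry is right.

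**Working it through.** **Does the text support each link?**

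1. Developer's staff do the entry: stated (Confidentiality, Relisten).
2. The source is paper: stated (Data Collection).
3. The arm is visible on the form: stated (Overview, Design, and Hypotheses of Study).
4. It is a main outcome: stated (Study Objectives, Statistical Analysis).
5. Blinding covers the patient only, as far as described (Data Collection).
6. Is the step addressed elsewhere? Confidentiality presents it as a privacy safeguard. Limitations of the Study covers selection, variation between professionals, time measurement and diligence of note review. Its statement that errors were analysed follows the passage on time measurement and note review, and survey entry is not mentioned.

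**Inputs for size** (Sample Size and Randomization): n = 400 per arm, σ = 1 point, target d = 0.25 point.

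The plan's own figure of 395.21 per group comes out as 4 × (1.645 + 0.84)² × 1² / 0.25² = 395.21. With factor 2, which reproduces the plan's time figure (2 × (1.645 + 0.84)² × (90/30)² = 111.15), the result would be 197.61. That mismatch is a separate matter and on the conservative side. Only n = 400, σ = 1 and d = 0.25 are used below.

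**Shift in the difference.** If a share p of forms in each arm is entered one point in the tool's favour (up in the tool arm, down in control), the shift is p × 1 + p × 1 = 2p.

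| Assumed p per arm | Forms per arm | Shift | Share of the 0.25 target |
|---|---|---|---|
| 2% | 8 | 0.04 | 16% |
| 5% | 20 | 0.10 | 40% |

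**Effect on the test when the tool has no true effect** (two-sided 0.05, normal approximation; the article does not state sidedness):

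- SE = 1 × √(2/400) = 0.0707
- Smallest significant difference = 1.96 × 0.0707 = 0.139
- False-positive rate = 1 − Φ(1.96 − shift/SE) + Φ(−1.96 − shift/SE)
  - shift 0.04: 8.7%
  - shift 0.05 (5% of forms in one arm only): 10.9%
  - shift 0.10: 29.3%

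The shares p are assumptions. The documents give no rate of unclear answers or of transcription error.

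**The case against.** The strongest reply is that transcribing closed 1–5 answers is largely mechanical. The article says the forms are transcribed. It does not say that Recog staff adjudicate unclear answers or discard forms. Free-text comments go to thematic analysis and cannot move a mean score. The worst case needs every affected form to err by a full point in the direction that suits the tool, in both arms, which is closer to systematic distortion than to ordinary slips. Even then the shift of 0.10 is below the 0.139 needed for significance, so it would not by itself be expected to produce a positive result. All of this stands, and it limits the likely size.

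A reader might also infer more than the article supports:

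- **That there is no check at all.** Double entry and verification against source are details an article commonly leaves to the full protocol. What can be said is that none is described.
- **That forms carry no identifier, so an entry cannot be traced to its form.** Anonymous collection and transcription without identifying data concern the patient's identity. Neither rules out a form number or a professional code. Planned results by professional suggest that some link may exist, and the survey itself is not shown.
- **That distortion could not be detected afterwards.** Data Collection mentions deletion only of the recordings. If the paper is kept, the forms can be re-keyed and compared.
- **That the data are biased.** Nothing shows that any form was or would be mis-entered.

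What remains is not an argument from silence. The article itself gives the task to the developer's staff and itself describes a form that reveals the arm.

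**Conclusion.** The point holds as a risk of bias built into the arrangement as written: the developer's staff enter one of the two main outcomes while able to see the arm. It is not a finding that bias occurred.

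Under assumed worst cases of 2% and 5% of forms per arm, each a full point in the tool's favour, the difference moves by 0.04 and 0.10, or 16% and 40% of the target. With no true effect, σ = 1, 400 per arm and a two-sided 5% test, the false-positive rate becomes about 9% and 29%. Realistic figures are probably smaller, because the items are closed and keying is simple. The case for changing the arrangement is that the exposure is avoidable at small cost, not that a large distortion is likely.

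**What to change.** **Remaining forms**, either of:

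- In Overview, Design, and Hypotheses of Study, replace the tool-only mark with a neutral code on every survey. The code must not be linked to patient identity and must not reveal the arm by its pattern. In Confidentiality, state that the investigators hold the code-to-arm key outside Recog until the file is locked. The code should not be recorded on the tool's own platform, since that would give the arm back to Recog.
- In Confidentiality, assign transcription to study personnel independent of Recog.

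**Forms already collected.** Cover the mark while the answers are keyed, or have independent study personnel re-key all or a sample from the paper, if it has been kept, and report the agreement with the file.

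**Cost.** Some data-entry time moves to the study team. Forms must be reprinted during recruitment: the Results section reports 318 of 800 enrolled by November 2024, leaving 482 at that date. The dataset would then contain two versions of the form, so the date of change must be documented, and the ethics committee may need to be notified. If recruitment has since finished, only the step for collected forms applies. Sample size and analysis do not change.

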### Ethical Considerations

This study was approved by the University Institute for Primary Care Research Jordi Gol Health Care Ethics Committee (Code 3/286-P). The research adhered to institutional guidelines for studies involving human subjects, including those requiring the recording of patient interactions and subsequent analysis. Written informed consent will be obtained from all participants before their inclusion in the study. Participation was entirely voluntary. No monetary or material compensation was provided to participants. All participants will complete a written informed consent. Upon arrival at the CAP, the Admissions administration staff will offer the patient the chance to participate in the study. The participant will be given the information sheet attached to the informed consent form, where he or she will be informed about the purpose of the study and the handling of the data. If the patient authorizes his or her participation, he or she must complete and sign the informed consent form and give it to the clinical professional with whom the consultation is to take place.

## Results

This study was preregistered on ClinicalTrials.org. Recruitment began in July 2024, and as of November 2024, a total of 318 patients have been enrolled at participating CAPs. The recruitment process is proceeding more slowly than expected and to ensure sufficient sample size the recruitment period has been extended until March 2025. This adjustment enables comprehensive data collection without compromising the study’s objectives.

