**Results:**

The protocol has been developed using the SPIRIT (Standard Protocol Items: Recommendations for Interventional Trials) checklist. Recruitment began in July 2024, and as of November 2024, a total of 318 patients have been enrolled. Recruitment is expected to be completed by March 2025. Data analysis will take place between April and May 2025, with results expected to be published in June 2025.

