### Sample Size and Randomization

To calculate the sample size, the 2 objectives that require such calculation are considered:

For the patient satisfaction surveys, proposed on a Likert scale from 1 to 5, we are faced with the problem of comparing independent samples. Assuming normality in the difference of the samples (a hypothesis that will be verified during the statistical tests), the formula for the determination of the required sample size is the following:

Where Z_α_ and Z_β_ represent the Z-table values for confidence level and test power, respectively, sigma is the SD of the (estimated) differences, and d is the effect size to be measured. For this study, standard values for α=.05 (95% confidence) and β=.8 (80% test strength) are selected, σ=1 is estimated as an extreme case to ensure that the results will be statistically significant, and d=0.25, as the minimum improvement we want to demonstrate. The result is n=395.21 for each group, so we set the number of patients to be analyzed to 400 with the AI-powered tool and 400 without the tool.For time-saving, applying a similar procedure with the same standard values, σ=90 seconds and d=30 seconds, we obtain n=111.15 for each group, so we set the number of consultations to be analyzed to 120 with the AI-powered tool and 120 without the tool.Since the groups are the same and there is no interconnection between the measurement of both objectives, it is possible to use the same consultations for both, and therefore the total number of patients required will be the larger of the two above, resulting in n=800 (400 patients with the AI-powered tool and 400 without the tool).The randomization was carried out in a simple format, given the sufficient sample size and the fact that the aim is to validate the hypotheses at a general level, although for information purposes the study also shows intermediate results stratified by type of consultation (first or follow-up) or by a health professional.

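### At the reported pace the extension to March 2025 very probably falls short of 800 patients, so the assurance of a sufficient sample needs an expected number and the power at that number

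*Protocol article*

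**What the plan says.** Sample Size and Randomization derives the target from patient satisfaction. It takes "standard values for α=.05 (95% confidence) and β=.8 (80% test strength) are selected" (the printed β is evidently the power), "σ=1 is estimated as an extreme case" and "d=0.25, as the minimum improvement we want to demonstrate". It then states that "The result is n=395.21 for each group" and rounds up, "resulting in n=800 (400 patients with the AI-powered tool and 400 without the tool"). These are patients to be analysed. Sidedness is not stated. For time saved, with σ=90 s and d=30 s, the section reports a similar procedure, 111.15 per group, set to 120.

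The abstract reports that "as of November 2024, a total of 318 patients have been enrolled", with recruitment having begun in July 2024. The Results section repeats this, says that recruitment is slower than expected, and gives the remedy: "to ensure sufficient sample size the recruitment period has been extended until March 2025". It adds that "This adjustment enables comprehensive data collection" and that the objectives are not compromised. Limitations of the Study still describes a study of 800. The article gives no projected total, no measure to raise the rate, and no revised target or power.

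**The concern.** After 318 patients, 482 remain, about 1.5 times the number already enrolled. The time left to March 2025 is, on most readings of the dates, not much longer than the time already used. The statement that the extension secures the sample therefore sits badly with the counts beside it. If 800 stays in print and is missed, the trial ends with an unexplained shortfall or a further unplanned extension. A closing decision made without a fixed rule is awkward here: the professionals know the allocation (Data Collection) and the developer's staff transcribe the surveys (Confidentiality), so a reader could not exclude that the data influenced when recruitment stopped.

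**Working it through.** **1. The plan's own figures.** With z = 1.645 and 0.84, (1.645 + 0.84)² = 6.1752.
- Satisfaction: 4 × 6.1752 × 1² / 0.25² = 395.21. This reproduces the printed value, with a factor of 4 and a one-sided 5% quantile.
- Time: 2 × 6.1752 × 90² / 30² = 111.15. This also reproduces, but with a factor of 2.

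The two calculations are not the same procedure. With the factor 2, satisfaction gives 2 × 6.1752 / 0.0625 = 197.6 per group one-sided, so 395.21 equals the one-sided total for two groups labelled as a per-group number. The standard two-sided formula gives 2 × (1.960 + 0.8416)² / 0.0625 = 251.2, or 252 per group.

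**2. Projection at a constant rate.** Only months are printed, so the days are assumptions. Projection = 318 × (days from start to close) / (days from start to count).

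| Start | Count | Close | Per week | Projected total |
|---|---|---|---|---|
| 1 Jul | 30 Nov | 1 Mar | 14.6 | 508 |
| 1 Jul | 30 Nov | 31 Mar | 14.6 | 571 |
| 15 Jul | 15 Nov | 31 Mar | 18.1 | 670 |
| 1 Jul | 1 Nov | 31 Mar | 18.1 | 706 |
| 31 Jul | 1 Nov | 31 Mar | 23.9 | 831 |

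Over 18 combinations (start 1, 15 or 31 July; count 1, 15 or 30 November; close 1 or 31 March) the range is 508 to 831. Seventeen fall below 800.

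For the mid-month case, 123 days have elapsed and 136 remain: 318 + 318/123 × 136 ≈ 670. Reaching 800 needs 482/136 × 7 = 24.8 per week against 18.1 observed, a ratio of 1.37.

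For comparison, the development phase of about 20 weeks in Overview, Design, and Hypotheses of Study implies 800/20 = 40 per week.

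**3. Power for d = 0.25, σ = 1, with n per group equal to half the total.**
- Article's calculation: Φ(√(n/64) − 1.645). At n = 395.21 this is Φ(0.84) = 80%, as stated.
- Standard two-sided: Φ(0.25/√(2/n) − 1.96).

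| Total | Article's calculation | Standard two-sided |
|---|---|---|
| 508 | 64% | 80% |
| 571 | 68% | 85% |
| 670 | 74% | 90% |
| 706 | 76% | 91% |
| 800 | 80% | 94% |

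These figures treat every enrolled patient as analysable and all observations as independent.

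**The case against.** The strongest reply is that this is a forecast and not a contradiction. The article does not promise 800 by March. It gives no monthly counts or centre start dates, and the elapsed period includes start-up and summer. On mid-month dates a 1.37-fold rise closes the gap, and one combination of dates reaches 831 with no rise at all. This stands, and it is why the conclusion is that 800 is very probably missed at a constant rate. A reader might infer that it cannot be reached; month-level dates do not support that.

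The second reply is that the stated harm largely disappears under the standard formula, which gives at least 80% power at every projected total. The time objective needs 240 consultations, fewer than the 318 already enrolled if the split is about equal and the recordings are usable. This also stands. A reader might infer that the trial will be underpowered for satisfaction. That follows only from the factor-4 calculation, which is itself in doubt.

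The opposite inference is equally tempting: that 2 × 252 = 504 patients suffice and no further enrolment is needed. The documents do not support that either. The 800 counts patients to be analysed and the 318 counts patients enrolled. Surveys returned anonymously to a box may not all come back, recordings with technical problems are excluded (Setting of the Study), and extreme values will be dropped (Limitations of the Study). The same section expects significant variance between professionals, and the calculation makes no allowance for clustering.

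Finally, an article may leave an accrual plan to the full protocol. But the point here concerns a positive assurance that the article's own counts do not bear out, not a missing detail.

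**Conclusion.** The point holds in a limited form. At a constant rate, recruitment by March 2025 very probably falls short of 800: about 670 in the mid-month case, 508 to 831 over plausible dates, with 17 of 18 combinations below target. The assurance of a sufficient sample is therefore not supported by the article's figures. On its own calculation, power at 571 to 670 patients is about 68% to 74% against the stated 80%. On the standard two-sided formula it is about 85% to 90%, so a loss of power is not demonstrated.

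The conclusion rests on a constant rate, assumed days within the printed months, equal groups, full analysability and independence. Losses and clustering would lower all of the power figures; by how much cannot be said, since no return rate or intracluster correlation is given.

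**What to change.** 1. In Sample Size and Randomization, correct the satisfaction calculation so that it uses the same formula as the time outcome, and state whether the test is one-sided or two-sided.
2. In that section, in Results and in Limitations of the Study, replace the unqualified 800 and the assurance with the number expected by the March 2025 close and the power at the number expected to be analysable. Say that unreturned surveys, excluded recordings and clustering by professional would lower that power.
3. Fix the exact closing date before any outcome is compared between groups.

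504 should not be adopted as a new target, and the text should not say that no extra enrolment is needed.

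The cost is one corrected calculation and a few sentences. The stated sample size will look less favourable, but the design does not change.
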